### Who will take informed consent? {26a}

A limited number of infectious disease physicians at each site will be responsible for obtaining informed consent from trial participants prior to treatment allocation. These physicians will receive specific training and instructions on how to follow protocol and how to collect and record data in the trial. The physicians will provide oral and written information about the study, any risks or benefits involved with participation and inform potential participants that termination from the study can be done at any time without explanation in accordance with the ethical approval. Written information will be provided after all eligibility criteria is fulfilled on days 1–5 from the initiation of EPE-active intravenous antibiotic. Recruiting physicians are asked to provide at least a few hours for each participant to contemplate their participation.

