### Criteria for discontinuing or modifying allocated interventions {11b}

There are no mandated criteria for discontinuing or modifying allocated interventions, but the patient and the treating physician may choose to do so at any time, upon which they will be asked to report timing and reason for non-adherence.

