### Plans to promote participant retention and complete follow-up {18b}

Since the follow-up is via telephone and done centrally, we expect that retention will be high. If the central outcome assessor cannot reach the participant, they will contact the recruiting physician who will check if the participant is deceased through the medical chart. Participants who are not reported dead and still cannot to be reached for the telephone interview follow-up will not qualify for analysis of the primary outcome or bacterial culture-related outcomes but can be assessed retrospectively from medical chart review regarding 28-day mortality, which is important for the evaluation of harm. We suspect that patients who deviate from the prescribed intervention will often be categorised as a negative outcome in the primary outcome assessment (e.g. new antibiotic prescribed), while some will simply be regarded as protocol violations. However, if a participant chooses to discontinue the trial, any collected data will be discarded, and the participant will only appear as a figure in the study flow chart.

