### Interim analyses {21b}

An interim analysis will be performed once half of the patients have been included (*n* = 165). Blinded data will be delivered by an independent statistician to the Data Monitoring Committee (DMC) who will then provide an allocation-blinded recommendation to the trial investigators whether to continue, hold or terminate the trial prematurely. The recommendation is based on safety and futility. Safety is based on three parameters, the number of possibly related serious adverse events, the number of early study drug discontinuations and the number of deaths within 28 days. It is difficult to provide fixed stopping criteria for safety since these events are expected to be very few, and the DMC have to assess frequency, severity and possible relationship to the study drug and give their best advice accordingly. Futility is defined as less than 5% probability of finding non-inferiority in the final analysis based on conditional power simulations as suggested by Bratton et al. [48]. The trial investigators will make the final decision whether to terminate the trial and will have to provide a written account to explain if they do not follow the recommendation from the DMC.

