### Methods in analysis to handle protocol non-adherence and any statistical methods to handle missing data {20c}

We will analyse the population both as intention-to-treat (ITT, i.e. as randomised), modified intention-to-treat (mITT, i.e. patient who took at least one dose of allocated study medication) and per protocol (PP, i.e. no major protocol deviations and missed a maximum of two doses of allocated study drug). We will only state non-inferiority if all three types of analyses provide concordant results [49]. If results are discordant, it will require a close examination of the data and could lead to either a statement of conditional non-inferiority or final uncertainty by the steering committee (SC).

All variables will be screened for frequency and type of missingness (i.e. missing completely at random, missing at random or missing not at random). Multiple imputation with chained equations will be used if missingness is above 5% in any variable included in the primary or secondary analysis. In the case of missingness, data with multiple imputation will be regarded as the primary analysis and complete case analysis will be performed as a sensitivity analysis.

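### Discarding all data of participants who leave the trial contradicts the as-randomised ITT set, and requiring ITT, mITT and PP to agree does not protect against the resulting bias

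*Protocol article*

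**What the plan says.** Section {18b} of the protocol article, on retention and complete follow-up, states that "if a participant chooses to discontinue the trial, any collected data will be discarded". All that remains of such a person is one number in the diagram of participant flow. The rule makes no exception for allocation, baseline data, outcomes or adverse events already recorded. The same section treats participants who cannot be reached differently: their 28-day mortality is still taken from the chart, because it matters for judging harm.

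Section {20c} plans three analysis sets. The first is "intention-to-treat (ITT, i.e. as randomised"; the others are a modified ITT set (at least one dose taken) and a per-protocol set. It then sets a safeguard: "We will only state non-inferiority if all three types of analyses provide concordant results". On missing data it says: "Multiple imputation with chained equations will be used if missingness is above 5% in any variable included in the primary or secondary analysis".

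Leaving the trial and stopping the drug are separate events. Section {26a} tells participants that "termination from the study can be done at any time without explanation in accordance with the ethical approval". For those who only stop or change the drug, section {11b} says "they will be asked to report timing and reason for non-adherence", and early discontinuation is itself a secondary outcome. The interim safety review in section {21b} uses possibly related serious adverse events, "the number of early study drug discontinuations and the number of deaths within 28 days".

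**The concern.** Leaving the trial happens after randomisation. Participants know their treatment, and the regimens differ: two oral drugs three times daily in the PAC arm, and in the control arm an expected 40% or so on once-daily intravenous ertapenem. The decision to leave, and the prognosis of those who leave, may therefore differ by arm. If their records are removed, the comparison is no longer between the groups as randomised.

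A non-inferiority conclusion is sensitive to this. Removing more failures from the PAC arm raises its observed cure rate and makes a false claim more likely. Removing more failures from control does the reverse. Because reasons for leaving need not be given and the data are gone, nobody could later tell which had happened. An analysis plan written later cannot repair this, since it cannot recover discarded data.

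**Working it through.** **Step 1: the passages side by side.** A participant who remains only as a flow-chart count has no record from which to be analysed. That participant is absent from ITT, although ITT is defined by randomisation alone, and also from mITT and PP. The three sets share the exclusion, so they can agree perfectly while all carry the same bias. Imputation is no clear remedy: discarding removes the baseline and partial outcome data that an imputation model would use, and a deleted record need not count towards the 5% trigger.

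**Step 2: the plan's own figure.** Section {14} states 90% power for 300 patients, with 93% cure, a 10-point margin and one-sided 2.5%. With 150 per arm and site ignored, SE = √(2 × 0.93 × 0.07/150) = 0.0295 and power = Φ(0.10/0.0295 − 1.96) = Φ(1.43) = 92.4%. Simulation with 30 sites of 10, ICC 0.1 and allocation not balanced within site gave 90.1–91.8%. The stated figure is reproduced and is not in dispute; it supplies the 150 per arm used below.

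**Step 3: size of the bias.** From the protocol: control cure 93%, margin 10 points, one-sided 2.5%, 150 per arm. Assumed, because the protocol gives no figure: true PAC cure of 83% over all randomised (exactly at the margin), withdrawal shares w_T (PAC) and w_C (control), and the cure rate c that the withdrawn would have had.

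- Observed cure after discarding: p′ = (p − w·c)/(1 − w), in each arm.
- Remaining size: n′ = 150(1 − w).
- SE = √[p′_T(1 − p′_T)/n′_T + p′_C(1 − p′_C)/n′_C].
- Probability of claiming non-inferiority = Φ[(p′_T − p′_C + 0.10)/SE − 1.96].

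Worked case, w_T = 5%, w_C = 0, c = 0: p′_T = 0.83/0.95 = 0.8737; difference = 0.8737 − 0.93 = −0.0563; n′_T = 142.5; SE = 0.0348; Φ(0.0437/0.0348 − 1.96) = Φ(−0.70) = 24.1%.

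| Withdrawn, PAC / control | Cure among withdrawn | Observed difference (points) | False non-inferiority |
|---|---|---|---|
| 0 / 0 | – | −10.0 | 2.5% |
| 3% / 0 | 70% | −9.6 | 3.2% |
| 5% / 0 | 70% | −9.3 | 3.8% |
| 3% / 0 | 50% | −9.0 | 4.6% |
| 5% / 0 | 50% | −8.3 | 6.9% |
| 3% / 0 | 0% | −7.4 | 10.7% |
| 5% / 0 | 0% | −5.6 | 24.1% |
| 5% / 2% | 0% | −7.5 | 11.2% |
| 3% / 3% | 0% | −10.3 | 2.0% |
| 0 / 3% | 0% | −12.9 | 0.3% |

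At 5% the PAC arm loses 0.05 × 150 = 7.5 patients, so a handful is enough. The last row shows the opposite direction. If both arms truly cure 93% and control alone loses 3%, all failures, observed control cure is 0.93/0.97 = 95.9% and the same formula gives power of 76.5% instead of 92.4%.

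**Step 4: safety data.** Section {22} requires serious adverse events to be reported from allocation to day 28. Under {18b}, events and early drug discontinuations recorded before a participant left would drop out of the trial dataset, and so out of the comparison between arms.

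**The case against.** Five points on the other side carry weight.

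- **Scope.** The rule covers leaving the trial, not stopping the drug. Intolerance or poor response will usually lead to a change of drug, which {11b} and {18b} handle separately and often as failure. A reader might infer that stopping treatment triggers deletion; the text does not say so. This stands, and it limits how many participants are affected.
- **Direction.** A reader might infer that the rule always favours non-inferiority. The documents do not support that. A participant who leaves because of daily intravenous visits is a control participant, and losing control failures works against PAC. This stands.
- **Size.** The 10.7–24.1% figures require every withdrawn patient to be a failure and all withdrawals to come from PAC. That is an extreme corner, not an expectation. The protocol expects high retention, and rare or balanced withdrawal has little effect. This stands, and is why the range is shown.
- **Safety.** A reader might infer that safety data are lost altogether and that deaths are hidden from the DMC. That goes too far. Reports already sent to the sponsor, the regulator or the DMC under {22} and {21a} probably survive there, and a patient who dies in the trial has not chosen to leave. What is lost is narrower: the contribution to the comparative dataset.
- **Consent.** The discard may reflect what participants were promised, and the consent form is not shown. However, neither the consent section {26a} nor the data-protection reference in {19} says that leaving requires erasing data already collected.

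The wider claim that the imputation plan as a whole cannot operate also fails: it still works for unreachable participants who remain in the dataset. None of this removes the conflict with ITT as randomised.

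**Conclusion.** The contradiction is real and lies in current text: the discard rule and the ITT definition cannot both be applied to a participant who leaves, and the three-set concordance rule gives no protection because all three sets share the exclusion. The size is unknown, since no withdrawal rate is given. With the assumptions in the working (true cure at the margin, 150 per arm, 3–5% withdrawal from PAC only), the 2.5% error becomes 3.2–3.8% at 70% cure among the withdrawn, 4.6–6.9% at 50%, and 10.7–24.1% at none. It is about 2.0% with balanced 3% withdrawal and below nominal when failures leave from control. The effect on safety is limited to events and drug discontinuations recorded before withdrawal leaving the between-arm comparison. The sentence should be changed promptly, because recruitment has begun and discarded data cannot be restored.

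**What to change.** Replace the sentence in {18b} with a rule on these lines:

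1. Data collected up to withdrawal are retained and analysed. Deletion happens only where the participant demands it and the law or the consent given requires it.
2. Withdrawn participants stay in the ITT set: as failure if a failure was recorded before they left, otherwise with a missing outcome handled by the method in {20c} and counted towards its 5% trigger.
3. Chart follow-up for death, readmission and antibiotics continues unless the participant objects.

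This reduces the bias but does not guarantee its removal: outcomes that are never obtained still depend on valid imputation. Withdrawals alone may not reach the trigger (5% of one arm is 7.5/300 = 2.5% overall), although the 10% loss for which the sample size allows would.

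The cost is an amendment to the protocol and the patient information. It may not cover participants who consented under the existing terms, so the report should state how many withdrew, in which arm, and how many records were deleted.

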### Data management {19}

All data entry will be done electronically, except for code keys and informed consent forms. The eCRF in the REDCap database uses data range checks. The primary outcome and secondary outcomes 2-4 will be double-checked retrospectively against the medical journal by the treating physician 30–60 days after randomisation. Individual patient data will be handled as ordinary chart records and will be kept according to the European General Data Protection Regulation (GDPR). All original records (i.e. code keys and consent forms) will be retained in a locked cabinet at each participating centres infectious disease department for 25 years to allow inspection by relevant authorities. The coded trial database will be maintained for 25 years if requested for revision. Standardised data management procedures can be provided on request from Clinical Trials Sweden—Forum South.

### Confidentiality {27}

At the time of randomisation, participants will be assigned a trial ID number which will be used on all the personal information containing documents (i.e., in consent forms and eCRF). The code key will be kept in a locked cabinet at each participating centre which can only be accessed by the limited number of physicians who can recruit patients. The coded information will be kept in an electronic database which requires two-step verification for login. When data from the study is published in a peer-reviewed medical journal, personal data will not be identifiable.

### Plans for collection, laboratory evaluation and storage of biological specimens for genetic or molecular analysis in this trial/future use {33}

Post-treatment urine and rectal specimens will be financed by the trial but sent to each participating centre’s microbiological laboratory and will be evaluated as per clinical routine and susceptibility testing according to EUCAST guidelines. Only culture positive findings of EPE are noted, and samples will be discarded after 2 weeks from collection without further analysis. Isolates from original urine and blood samples collected from participants at the coordinating microbiology centre (Lund) will be saved in the microbiology department’s freezer storage for preliminary future study of PAC MIC.

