**Discussion:**

If the combination of pivmecillinam and amoxicillin/clavulanic acid is found to be non-inferior to the control drugs there are potential benefits in terms of tolerability, frequency of interactions, outpatient treatment, side effects, nosocomial infections and drive for further antimicrobial resistance compared to existing drugs.

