#### Secondary objectives

To compare participants’ perception of treatment tolerability on a 1–10 scale.To compare the incidence of early study drug discontinuation between groups.To compare the incidence of additional antibiotic subscriptions (for UTI) within 28 days between groups.To compare re-admission to hospital (due to UTI-related symptoms) within 28 days between groups.To compare the incidence of drug-related serious adverse events (SAE) within 28 days between groups.To compare the all-cause mortality within 28 days between groups.To compare the recurrence prevalence of EPE (phenotypically same species) in urine cultures 10 +/− 2 days after antibiotic treatment between groups (i.e. microbiological cure).To compare the prevalence of EPE or carbapenemase-producing bacteria in faecal cultures 10 +/− 2 days after antibiotic treatment between groups.

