#### Secondary outcomes

Participants’ perception of treatment tolerability on a 1–10 scale.Early study drug discontinuation.Additional antibiotic subscriptions (for UTI) within 28 days from randomisation.Proportion of patients re-admitted to hospital (due to UTI symptoms) within 28 days from randomisation.Drug-related serious adverse events within 28 days from randomisation.All-cause mortality within 28 days from randomisation.Growth of EPE (phenotypically same species) in urine culture (10^3^ CFU/mL) 10 +/− 2 days after antibiotic treatment.Growth of EPE or carbapenemase-producing bacteria in faecal cultures 10 +/− 2 days after antibiotic treatment.

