## Data collection and management

### Plans for assessment and collection of outcomes {18a}

Baseline data and allocation will be entered into the REDCap database using a short and study-specific electronic case report form (eCRF) directly when assessing eligibility and assigning allocation by the physician who recruited the participant. The trial investigators will instruct a limited number of physicians at participating centre how to access and fill out the eCRF and provide a step-by-step guide and contact information for technical assistance. The primary outcome and the secondary outcomes 2-4 will be assessed using a semi-structured interview with a trial-specific guideline and entered into a separate part of the REDCap eCRF. The first 10 participants’ interview responses will be checked for conformity between at least two study nurses. The remaining secondary outcomes will be assessed retrospectively through medical chart review and from microbiological results by the recruiting physician at 30–60 days after the patient was allocated and then entered into a final separate part of the eCRF. The retrospective chart review will also serve as a sensitivity analysis to the telephone interview for the primary outcome and the secondary outcomes of early drug discontinuation and further antibiotic prescription. A copy of the REDCap eCRF (English) and semi-structured interview guideline (Swedish) can be sent on request.

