## Abbreviations

AE: Adverse events
AMR: Antimicrobial resistance
BSI: Bloodstream infections
DMC: Data Monitoring Committee
eCRF: Electronic case report form
eGFR: Estimated glomerular filtration rate
EPE: ESBL-producing Enterobacterales
ESBL: Extended spectrum beta-lactamase
EUCAST: European Committee of Antimicrobial Susceptibility Testing
FDA: U.S. Federal Drug Administration
GDPR: European General Data Protection Regulation
GEE: Generalised estimated equations
ID: Infectious disease
ITT: Intention-to-treat
mITT: Modified intention-to-treat
OPAT: Outpatient parenteral antimicrobial therapy
PAC: Pivmecillinam and amoxicillin/clavulanic acid
PACUTI: Pivmecillinam with amoxicillin/clavulanic acid for step down oral therapy in febrile UTIs caused by ESBL-producing Enterobacterales
PP: Per protocol
RCT: Randomised controlled trial
SC: Trial steering committee
TMX: Trimethoprim–sulfamethoxazole
UTI: Urinary tract infections
SUSAR: Suspected unexpected serious adverse reaction

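### Section {33} notes only EPE from the follow-up cultures, but secondary outcome 8 also counts carbapenemase producers, so their capture is not assured

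*Protocol article*

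**What the plan says.** The eighth secondary objective is "To compare the prevalence of EPE or carbapenemase-producing bacteria in faecal cultures", assessed 10 ± 2 days after antibiotic treatment. The matching entry under Secondary outcomes reads "Growth of EPE or carbapenemase-producing bacteria in faecal cultures". The statistical methods section {20a} treats this as one binary outcome, analysed by GEE and reported as a risk difference.

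Section {33} describes the post-treatment urine and rectal specimens. They go to each centre's own laboratory and "will be evaluated as per clinical routine and susceptibility testing according to EUCAST guidelines". The next sentence is "Only culture positive findings of EPE are noted, and samples will be discarded after 2 weeks from collection without further analysis". The abbreviation list gives "EPE: ESBL-producing Enterobacterales".

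Section {18a} assigns outcomes 2–4 to the telephone interview and then says: "The remaining secondary outcomes will be assessed retrospectively through medical chart review and from microbiological results by the recruiting physician". It places this review between 30 and 60 days from allocation. Outcome 8 is among these remaining outcomes.

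**The concern.** The outcome definition has two ways to be positive, joined by an or. The only section that says what is noted from the follow-up cultures admits one of them. This is a restrictive instruction, so it differs from detail left to an analysis plan: an analysis plan cannot analyse a finding that sites were told not to note.

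Outcome 8 is the only outcome in the trial that names carbapenemase producers. Table 1 expects ertapenem, a carbapenem, in about 40% of controls, and the abstract lists among the potential benefits of the combination a lower "drive for further antimicrobial resistance compared to existing drugs". If {33} is followed, outcome 8 becomes EPE carriage alone under a label that promises more. Readers of the results could take it as evidence on carbapenemase carriage that was never collected.

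**Working it through.** No power, alpha or event figure is involved, and the plan states no number to reproduce. The check sets the outcome definition against the recording rule for each kind of participant. It takes the rectal specimens of {33} to be the source of the faecal cultures in outcome 8.

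| Growth in the follow-up faecal culture | Outcome 8 as defined | Result if {33} is followed |
|---|---|---|
| Neither | Negative | Negative |
| EPE only | Positive | Positive |
| EPE and a carbapenemase producer (same isolate or two) | Positive | Positive |
| Carbapenemase producer that is not EPE | Positive | **Negative** |

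Only the last row is misclassified. In the third row the composite is scored correctly, but {33} does not ask for the carbapenemase finding to be noted.

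**Can an omission be repaired later?** Count from allocation and take the longest case, in which all 10 treatment days follow allocation:

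- Latest sampling day: 10 + 12 = day 22.
- Discard two weeks later: 22 + 14 = day 36.
- Chart review window: days 30 to 60. From day 36 to day 60, that is 24 of the 30 days, the specimen is already gone.

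A test that was never done therefore usually cannot be added at chart review. A test that was done and reported can still be read, because {33} discards samples and says nothing about discarding reports.

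**How many participants?** The protocol gives no carriage rates, so only an illustration is possible. Let N be the number with a culture, c the proportion carrying a carbapenemase producer, and e the proportion of those carriers who also grow EPE. Then misclassified = N × c × (1 − e).

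- With N = 330 (the maximum) and assumed c = 1–3%, carriers number 330 × 0.01 = 3.3 to 330 × 0.03 = 9.9.
- With assumed e = 50%, the misclassified number 3.3 × 0.5 = 1.7 to 9.9 × 0.5 = 5.0, so about 2 to 5 people.
- Over the whole range of e, the number runs from 0 (every carrier also grows EPE) to about 10 (none does, at c = 3%).

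**Carbapenem exposure.** With 330/2 = 165 controls, 0.40 × 165 = 66 are expected on ertapenem. This is the size of the exposed group; it is not a count of lost results.

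**The case against.** The strongest reply is that {33} is an item about specimens and is neither the outcome definition nor the data-entry specification. The specimens receive routine work-up with susceptibility testing, and {18a} has the recruiting physician enter outcome 8 from the laboratory results. A carbapenemase finding that the laboratory reports could reach the eCRF by that route. The eCRF is not shown and may already have a field for it. This stands, and it is why the point is that capture is not assured.

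It does not remove the conflict. The wording in {18a} is general and that in {33} is specific and restrictive, so what is recorded depends on which sentence each of up to 29 clinics follows. Section {17a} also says that the physician assessing outcomes 2–8 is not blinded, which makes discretionary recording a weak basis for comparing arms. Nor do the documents say whether routine work-up looks for carbapenemase producers in rectal samples.

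The text of the footnote attached to EPE in the inclusion criteria is not shown, so a wider definition cannot be excluded. Even a wider one would not clearly cover carbapenemase producers outside Enterobacterales, and outcome 8 speaks of bacteria in general.

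A reader might infer three stronger points that the documents do not support:

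- **That carbapenemase producers cannot be captured at all.** The route in {18a} contradicts this.
- **That outcome 8 is the protocol's designated measure of further resistance.** The protocol lists resistance as a potential benefit and never ties it to this outcome.
- **That persisting EPE would mask a carbapenemase signal in the composite.** All participants enter with EPE, so this is plausible, but any figure for it would rest on assumed rates.

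**Conclusion.** The conflict is real and lies in the current text: {33} restricts what is noted to EPE, while the objectives and outcomes sections define outcome 8 to include carbapenemase producers. If {33} governs, a participant carrying only a non-EPE carbapenemase producer is scored negative on an outcome that defines that participant as positive.

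The consequence is limited. The sample size section declares the secondary objectives exploratory, and the non-inferiority conclusion does not depend on outcome 8. On the assumed rates the misclassified would be few, and an arm difference in such small counts would carry little information even with complete recording. The reason to act is that the outcome's label would promise a carbapenemase result that sites were told not to note, in a trial that expects a carbapenem in about two fifths of controls. The conclusion assumes that EPE carries the meaning in the abbreviation list and that no unseen eCRF instruction already overrides {33}.

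**What to change.** Amend {33} so that, for the follow-up faecal (rectal) culture, growth of EPE and growth of carbapenemase-producing bacteria are both noted, each in its own eCRF field if not already present. The urine culture needs no change, because outcome 7 concerns EPE only. Report the number with each finding by arm beside the composite, and state from what date both were recorded. For participants already followed up, existing laboratory reports can be checked for carbapenemase findings.

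If sites will not record carbapenemase producers, the alternative is to restrict outcome 8 and its objective to EPE and to draw no conclusion about carbapenemase carriage.

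The cost is a change of wording, at most one added field and an instruction to sites and laboratories. No extra visits, samples or participants are needed. If a laboratory's routine work-up does not look for carbapenemase producers, there would be some added laboratory work, which the documents do not allow one to cost. The change is best made while recruitment continues, since discarded samples cannot be cultured again.
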